Adherence will be also encouraged through regular communication and guidance by the general practitioners as part of the study protocol. There will be no formal follow-up conducted after the intervention. However, reasons for participant discontinuation will be systematically collected to understand the factors influencing dropout rates.

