###  Participants

 Assuming that the hospitalization rate in the patient group before the intervention is approximately 20 percent [2] with a potential of reduction to 15 percent during intervention (a reduction of 25 percent), with a power of 90 percent and a significance level of 0.05, the calculated sample size is 1,210 patients for the intervention group [18]. To address sample attrition due to heightened mortality in the research group as well as other unforeseeable drop-outs, about 25 percent additional patients should be recruited, resulting in a total sample size of *n* = 1,500 participants in the intervention group, with at least the same number of controls to be drawn. GPs will be recruited through outreach by the KV, which in turn will recruit eligible participants for the study. Alternatively, the participants will be recruited by a study physician to relieve the GPs. The informed consent will be obtained from the participants by either their GP or the study physician. The intervention group will be derived from eligible insurees of the participating health insurance companies, who are 60 years or older, reside in Berlin in their own home, receive support from a caregiver, and have been either officially granted “care level” 1 or higher, have applied for it or been assessed by their GP as needing “care level” 1 or higher. In Germany, five “care levels” represent a scale used to classify the level of care needed by individuals requiring long-term care. The respective care level determines the subsidies those individuals receive through their nursing care insurance provider. Participants can withdraw their consent to participate in the study anytime. If participants stop meeting the inclusion criteria listed above at some point, e.g. leave their participating insurance company, they will be excluded from the study.

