**Health insurance perspective**			
Utilization: Hospital stays and emergency responses	Number of hospital stays/ emergency responses	Claims data	primary
Utilization: Ambulatory-care sensitive hospital stays and emergency responses	Ambulatory-care sensitive diagnoses	Claims data	primary
Utilization: ambulatory resource allocation	Ambulatory medical utilization	Claims data	secondary
Cost: New form of healthcare	All costs directed towards the new form of healthcare	Diary and claims data	primary
Cost: Comparison of new form of healthcare versus standard care	Comparison with saved costs of standard care	Diary and claims data	primary

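### Excluding participants who lose eligibility after entry, with no matching rule stated for control group 1, can produce a spurious reduction in hospital stays

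*Protocol article*

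**What the plan says.** The Participants section sets the entry criteria: cover by a participating insurer, age 60 or over, a granted, requested or GP-assessed care level of at least 1, and that people "reside in Berlin in their own home, receive support from a caregiver". The same paragraph then says that if participants "stop meeting the inclusion criteria listed above at some point, e.g. leave their participating insurance company, they will be excluded from the study". Leaving the insurer is given only as an example, so the sentence covers every criterion.

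The primary utilization outcome in Table 1 is "Number of hospital stays/ emergency responses", taken from claims. Control group 1 is drawn from the insurers' own records and matched by propensity score. The matching variables named under Analysis (Health insurance perspective) describe the period before the study and do not mention home residence or a caregiver. No rule for leaving control group 1 during follow-up is stated. The Limitations section discusses selection into the study, not removal after entry.

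**The concern.** Home residence and caregiver support can both end as a result of a hospital stay. A rule that removes people when either ends therefore selects the intervention group on something the primary outcome can cause. Those removed would then tend to have more stays than those who remain.

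If control group 1 keeps its equivalent people, the comparison favours the intervention even when it has no effect. Caregiver loss is the clearest source of imbalance, because claims are unlikely to record it. At stake is whether a lower count of stays can be credited to the programme.

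**Working it through.** **The plan's own figure.** The inputs are a "hospitalization rate in the patient group before the intervention is approximately 20 percent", a fall to 15 percent, and the test "with a power of 90 percent and a significance level of 0.05". For two proportions, two-sided, the pooled-variance formula gives

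(1.960 × √(2 × 0.175 × 0.825) + 1.282 × √(0.20 × 0.80 + 0.15 × 0.85))² / 0.05² = 1,212 per group.

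The unpooled formula gives 1,209. The stated 1,210 reproduces and is not in dispute. Recruiting 1,500 allows for a loss of 1 − 1,210/1,500 = 19.3%.

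**Assumptions for the size of the bias.** The document gives no exit probabilities, so these are assumed:
- No true effect; one year of follow-up (by design, follow-up runs from 6 to 24 months).
- Stays are Poisson given a personal rate; rates vary as a gamma with dispersion 1 and mean *m*.
- Each stay has chance *p* of ending eligibility, with *p* = 2%, 5% or 10%; write *s* = 1 − *p*.
- *m* = 2 a year, the average in the Introduction (Background), or *m* = −ln(1 − 0.20) = 0.223 a year, reading the 20 percent planning rate as an annual risk.
- The rule acts in the intervention group only.

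**Formulas.**
- Share excluded within the year: 1 − 1/(1 + *mp*).
- Rate ratio if excluded people are dropped entirely: *s*/(1 + *mp*).
- Rate ratio if data are kept to exit: expected stays are *m*/(1 + *mp*) and expected person-time is ln(1 + *mp*)/(*mp*). Dividing these, and then by *m*, gives *mp*/[(1 + *mp*) ln(1 + *mp*)].

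Example with *m* = 2 and *p* = 10%: dropped entirely, 0.90/1.20 = 0.750; kept to exit, 0.20/(1.20 × 0.1823) = 0.914.

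| *p* | Excluded, *m* = 2 | Dropped, *m* = 2 | Kept to exit, *m* = 2 | Dropped, *m* = 0.223 | Kept to exit, *m* = 0.223 |
|---|---|---|---|---|---|
| 2% | 3.8% | 0.942 | 0.981 | 0.976 | 0.998 |
| 5% | 9.1% | 0.864 | 0.954 | 0.940 | 0.994 |
| 10% | 16.7% | 0.750 | 0.914 | 0.880 | 0.989 |

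A simulation of 400,000 people with whole-person deletion agrees with the two dropped columns to within 0.002.

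**Check on the planning scale.** Take a true risk of 20% in both groups and 1,500 enrolled in each. Remove a share *f* of the intervention group whose risk is RR times that of those retained. The apparent risk is 0.20/((1 − *f*) + *f* × RR).

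| *f* | RR | Apparent risk | Relative reduction | Chance of a significant result |
|---|---|---|---|---|
| any | 1 | 20.0% | 0% | 5% |
| 5% | 2 | 19.0% | 4.8% | 10% |
| 10% | 2 | 18.2% | 9.1% | 23% |
| 10% | 3 | 16.7% | 16.7% | 63% |

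If nobody is removed, or the same rule acts on controls with equal *f* and RR, this distortion is zero.

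**The case against.** The strongest reply is that the text ends participation and says nothing about the analysis. The rule sits under Participants next to withdrawal of consent. Its only example is an administrative event that ends access to claims anyway. Handling of data before exit is commonly left to an analysis plan, which is not shown. This stands in part: the document does not say that earlier claims are discarded, so whole-person deletion is a worst case. With data kept to exit, the bias shrinks, and at the planning rate it nearly vanishes. It does not remove the ambiguity, because the phrase used is exclusion from the study and no other end of follow-up is given.

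A reader might infer four stronger things that the documents do not support.

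- *That everyone who deteriorates is removed.* A hospital stay does not end eligibility, and neither does a higher care level. Only deterioration that ends home living or caregiver support does.
- *That the rule is one-sided by design.* The article is silent on controls. The nursing-care and short-term-care claims listed under Data sources may show moves to residential care in control group 1, so the same rule could be applied there. The asymmetry is firm only for caregiver loss.
- *That deaths count as successes.* The article plans for "To address sample attrition due to heightened mortality in the research group" and lists no mortality outcome, but the exclusion rule does not govern death, and deaths occur in both groups. Showing deaths beside admissions is a sound addition; it is not proof of bias.
- *That claims collection stops at exit.* The statement "There will be no formal follow-up conducted after the intervention" stands in a paragraph on adherence and does not say this. The next sentence says that reasons for discontinuation are collected.

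**Conclusion.** The concern holds as a badly fixed rule: read as written and carried into the primary comparison, it can produce a reduction in stays that the programme did not cause. The true size cannot be known from the document. The illustrations span rate ratios from 0.75 to about 1.00, depending on how often a stay ends eligibility, the underlying rate of stays, and whether data before exit are kept.

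The value 0.75 invites the inference that the bias could equal the whole planned 25 percent reduction. That needs entire deletion, one group only, a 10% exit chance per stay and 2 stays a year together. It also pairs the background rate with a target set on the 20 percent planning rate. At 0.223 stays a year, the lowest ratio in these illustrations is 0.88.

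The direction is also an assumption. If those excluded had fewer stays than those retained, the bias would reverse.

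**What to change.** Separate leaving the programme from leaving the analysis, and state this for the primary claims comparison:

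- Every enrolled participant stays in the comparison from the index date until death, leaving the insurer, withdrawal of consent to data use, or study end.
- A move out of the home or loss of a caregiver does not end claims follow-up.
- The same end-of-follow-up rule applies to control group 1.
- Stays are analysed per person-time.
- Exclusions by reason, and all-cause deaths in both groups, are reported beside the primary result.

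This costs wording and programming. The claims and insurer membership data are already planned, and the 1,210 does not change. The small downside is that time off the programme slightly dilutes the effect. With 36 participants enrolled at submission, the rule can be settled early, and it should be fixed before the planned interim evaluation.

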###  Study period

The study period is designed to take place within eight quarters (24 months). During the first six quarters (18 months), the intervention group will be gradually recruited for the new form of healthcare, so that individuals who are added at the end of the recruitment period can utilize the new form of healthcare for at least two quarters (6 months). For the control group 1 and the operationalization of control variables, the claims data of the health insurance companies from a pre-observation period of eight quarters before entry into the new form of healthcare will be used. The surveys on the secondary endpoints take place at the beginning of the intervention (weeks 2-4) and after 3 to 6 months during the intervention. The control group 2 is surveyed at a congruent time interval. Figure 2 illustrates the planned data collection period and the cumulatively increasing sample size of the intervention group.

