#### Patient perspective

 On the patient level, health, well-being, and care dependency will be evaluated in a pre-post-design, using data from the intervention group as well as the control group 2 (*n* = 300). Seven questions compiled on the basis of clinical experience will be used to assess general health. The participants of the intervention and control group 2 will be asked weekly about falls, pain, urinary excretion, restlessness, shortness of breath, dizziness, and an open-ended question about any health problems experienced within the last seven days. The Quality of Life-Alzheimer’s Disease (QoL-AD) [23–26] is used to assess cognitive functioning in week 2-4 and 3-6 months after starting participation. Within 13 items, it covers physical health, energy, mood, living situation, memory, family, marriage, friends, chores, joy, money, own self, and life in general. QoL-AD possesses a good content, criterion concurrent and construct validity, as well as an excellent interrater reliability (Cohen's κ
> 0.70) and internal consistency (Cronbach's α
= 0.82) [24].Quality of life will be assessed using the Wellbeing measures in primary health care (WHO-5) questionnaire, containing five questions about mental well-being, like being in a good mood, feeling energetic, or being interested in daily life [27–29]. WHO-5 has satisfactory psychometric properties, both in terms of reliability (e.g. internal consistency α
=.92, split-half reliability *r*_*tt*_= .87), construct and factorial validity [29]. The Oslo social support scale (OSSS-3) will be used to assess social support through three questions about relationships with close individuals and the availability of neighborly help [30, 31]. Its predictive and construct validity is reported to be good, while internal consistency (α = .640) is acceptable [30]. Moreover, the UCLA Loneliness Scale is added to measure loneliness within 20 items, evaluating topics like social isolation, companionship, and perceived social support [32]. Existing validation studies come to favorable assessments with regard to criterion, convergent and discriminant construct validity, as well as reliability (retest reliability >.70, internal consistency α
=.89, split-half reliability *r*_*tt*_=.85) [32]. The WHO-5 questionnaire, OSSS-3 and the UCLA Loneliness Scale will be conducted in week 2-4 as well as 3-6 months after beginning to participate.

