Care dependency will be assessed using the Barthel-Index [33, 34]. Here, ten activities of daily living are assessed regarding the capability of conducting them independently. Participants will conduct the assessment in week 2-4 and 3-6 months after enrolment into the study.

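### The 'pre' value of five secondary patient scales is measured in weeks 2-4 of the intervention, so any early change is absorbed into the baseline

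*Protocol article*

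**What the plan says.** The Study period section sets the general schedule: "The surveys on the secondary endpoints take place at the beginning of the intervention (weeks 2-4) and after 3 to 6 months". It adds that control group 2 is surveyed at matching intervals.

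The Patient perspective section under Outcomes gives the same timing scale by scale:

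- QoL-AD "is used to assess cognitive functioning in week 2-4 and 3-6 months after starting participation".
- The battery of WHO-5, OSSS-3 and UCLA-LS "will be conducted in week 2-4 as well as 3-6 months after beginning to participate".
- For the Barthel-Index, "Participants will conduct the assessment in week 2-4 and 3-6 months after enrolment into the study".

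The purpose of the two surveys is stated in the same section: "health, well-being, and care dependency will be evaluated in a pre-post-design, using data from the intervention group as well as the control group 2". The Patient perspective section under Analysis repeats that this is a pre-post comparison. It names age, gender and education as covariates and leaves the regression model open.

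One set of items runs on a different schedule: "The participants of the intervention and control group 2 will be asked weekly about falls, pain, urinary excretion, restlessness, shortness of breath, dizziness", plus an open question.

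The only data described as coming from before entry are claims data, covering eight quarters. The article describes no earlier measurement of the five scales.

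**The concern.** A pre-post comparison with an untreated group rests on the first value being unaffected by the intervention. Here it is taken two to four weeks in. According to the Intervention section, health status is recorded in the diary and reviewed by participant, caregiver and physician even while the participant is stable. Exposure to that part of the programme can therefore precede the first survey.

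The matching schedule in control group 2 does not cure this. It aligns the calendar, but only the intervention group can be changed by the intervention in those weeks.

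The first score also carries more weight here than it would in a randomised trial. Control group 2 is drawn from people insured elsewhere, and few covariates are named, so the first score is a main safeguard against groups that differ at the start. Better health, quality of life and care needs are stated aims in the Objective section, and no later analysis can recover a baseline that was never collected.

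**Working it through.** **The plan's own figure.** The article gives no figure on this point. Its one calculation, 1,210 patients for 20% versus 15% hospitalisation, reproduces: (0.20×0.80 + 0.15×0.85) × (1.960 + 1.282)² / 0.05² gives 1,209 with unpooled variance, and the pooled form gives 1,212. It concerns the primary outcome and does not enter what follows.

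**Inputs.** First survey at t0 = 2 to 4 weeks. Follow-up at 3 to 6 months, taken as T = 13 to 26 weeks. The shape of the effect over time, f(t), is not given and has to be assumed.

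**Formula.** For a change-score contrast, the share of the follow-up effect already in the 'pre' value is f(t0)/f(T). If the model instead adjusts follow-up for the first score with slope b, the deduction is b times that share.

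**Linear onset (assumed), f(t) proportional to t:**

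| First survey | Follow-up week 13 | Follow-up week 26 |
|---|---|---|
| Week 2 | 2/13 = 15.4% | 2/26 = 7.7% |
| Week 4 | 4/13 = 30.8% | 4/26 = 15.4% |

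**Late onset (assumed), f(t) proportional to t²:** (2/26)² = 0.6% to (4/13)² = 9.5%.

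**Early, levelling-off onset (assumed), f(t) = 1 − 2^(−t/h):** the contrast keeps [f(T) − f(t0)]/f(T). With a half-life h of 8 weeks it keeps 57% (t0 = 4, T = 13) to 82% (t0 = 2, T = 26), so 18% to 43% is absorbed. With h = 2 weeks it keeps 24% to 50%.

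**What this could mean for power (illustration only).** Assume full groups of 1,500 and 300, no attrition, and effects in SD units of the change score. The difference detectable with 80% power, two-sided at 0.05, is (1.960 + 0.842) × √(1/300 + 1/1,500) = 0.177 SD. If the baseline absorbs 7.7%, 15.4% or 30.8% of a true difference of that size, power falls to 73%, 66% or 49%.

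**With an unexposed baseline** the absorbed share is 0% under every shape.

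**Direction.** Let the early effect be e and the follow-up effect be d. The pre-post contrast estimates d − e. If e is a benefit, the result is biased toward no effect. If e is a burden that has faded by follow-up, d − e exceeds d and looks like improvement.

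**The case against.** The strongest reply is that little may have happened by week 4. The care network is triggered by events: the general practitioner is contacted first under standard care, and the network is activated only if that physician cannot be reached. Nothing shows that many participants would have had such an event by then. The sections also start the clock variously at intervention, participation and enrolment, and the article does not say when the diary is activated relative to enrolment. This stands in part. Early exposure to the diary is documented, but early exposure to the network is not. The Study period section nevertheless places the first survey within the intervention.

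It can also be said that the magnitude is assumption throughout. That is correct, and an event-driven effect could build late and lose less than the linear range.

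Three stronger readings may tempt a reader, and the article does not support them:

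- **Early drop-out distorts the baseline.** Someone lost before week 2 would also lack the month 3-6 value, so would be outside the observed change set under either schedule. No early drop-out rate is given; the 25 percent allowance covers the whole study and was set for the primary sample size.
- **Nearly all of the effect is lost.** That needs an immediate and complete effect on social support, loneliness and daily activities, for which the article gives no basis.
- **The wide follow-up window is a fault in itself.** How to handle the time between surveys is a modelling choice, and the regression model is left open for a statistical analysis plan that is not shown.

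**Conclusion.** The point holds in a limited form. The first QoL-AD, WHO-5, OSSS-3, UCLA-LS and Barthel values are on-intervention values used as the 'pre' side of a comparison with an unexposed, non-randomised group. The timing is the same in every section that mentions it, so it is a design feature and not a slip in one sentence.

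The size cannot be derived from the article. Under an assumed linear onset, 8% to 31% of the follow-up effect is absorbed; a late onset gives less, an early levelling-off onset more. An early benefit makes the result conservative, but an early burden that fades would flatter the intervention, so the bias cannot be assumed to be safe.

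A reader might extend this to all patient outcomes or to the trial's main result. Neither follows. The seven general-health questions are asked weekly and are not tied to weeks 2-4. The five scales are secondary, and the claims-based primary outcomes have a true pre-period.

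**What to change.** - **Participants not yet started:** give the first survey after consent and before the diary is activated, for example through SoSci Survey, which is already in use. Set the matching time point in control group 2.
- **Participants already enrolled:** keep the week 2-4 value, flag it, and run a sensitivity analysis without these participants. At submission on November 17, 2024 they numbered 36 of the planned 1,500 (2.4%), with recruitment open until June 30, 2025.
- **Wherever no pre-activation value exists:** do not describe the week 2-4 value as a pre-intervention baseline. If recruitment has closed, this is the part of the fix that remains.

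**Cost.** No new instrument or staff is needed. The start-up contact becomes longer by about 13 + 5 + 3 + 20 + 10 = 51 items. That burden is real, because study physicians are already used to relieve general practitioners at recruitment; online completion between consent and activation would limit it. Those already enrolled will have a baseline on a different footing from the rest.

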###  Data sources

The data for the evaluation will be gathered from two main data sources. Firstly, various reports will be generated from the digital interactive health diary. These reports will encompass health-related basic data entered by participants, their caregivers, and their primary care physicians, such as current condition, diagnoses, therapies, medication plans, level of care needed, allergies, and measured vital parameters. Additionally, questionnaires for process evaluation and evaluation of health and quality of life will be collected via the digital interactive health diary as well as via the online platform SoSci Survey. Furthermore, all data for the STH event will be extracted through digital interactive health diary reports for the evaluation of utilization patterns and costs, as well as for process evaluation.

As a second data source, data from the health insurance companies will be utilized (enrollee data, claims data concerning sick pay, nursing care, short-term care, outpatient and inpatient cases, ambulance services, prescription of medicinal products, medical devices, and aids). This will be used to establish the control group 1 and to obtain data for comparing the new form of healthcare with standard care.

The reports from the diary are continuously accessible in pseudonymized form by the evaluating parties. Each evaluation party receives only the data necessary for their specific research questions. For the evaluation utilization patterns and costs, it is necessary to merge the data from the diary with the enrollee and billing data from the health insurance companies. This is because treatments provided by the mobile medical on-call service within the framework of STH events are partly reimbursed and documented through STH project funds and partly through statutory health insurance.

Data collection forms cannot be provided here. However, all variables and their response formats are described within the protocol.

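### The timing of the second patient survey is worded inconsistently, and on one reading people who stop the programme early lose their post value by routes that control group 2 does not have

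*Protocol article*

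**What the plan says.** Four parts of the protocol article bear on whether someone who stops the programme still gives a second set of patient-reported outcomes.

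- **Study period.** The surveys are placed "at the beginning of the intervention (weeks 2-4) and after 3 to 6 months during the intervention. The control group 2 is surveyed at a" matching interval.
- **Intervention, closing paragraph.** "There will be no formal follow-up conducted after the intervention". The next sentence names one thing gathered from people who stop: "reasons for participant discontinuation will be systematically collected to understand the factors influencing dropout rates". No outcome measurement is mentioned.
- **Participants.** People who no longer meet the listed criteria are removed: "e.g. leave their participating insurance company, they will be excluded from the study". The list is that of the intervention group and includes living at home in Berlin, having a caregiver and belonging to a participating insurer.
- **Outcomes, Patient perspective.** The second QoL-AD, WHO-5, OSSS-3 and UCLA loneliness assessments are counted from the start of participation, and the second Barthel assessment from enrolment. Continued use of the diary is not mentioned.

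On the route, the Data sources section says that the questionnaires "will be collected via the digital interactive health diary as well as via the online platform SoSci Survey". These outcomes are secondary. They are compared pre-post using the intervention group and control group 2 (n = 300).

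**The concern.** The diary delivers the intervention and is also one of the survey routes. If the second survey is due only while a person is in the programme, and nothing but a reason is recorded when a person stops, then stopping before month 3-6 ends outcome measurement. Control group 2 has no programme to stop. The exclusion rule adds a second route: a participant who loses the caregiver or changes insurer is removed, and no equivalent rule is stated for control group 2.

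People lost in these ways may well differ in quality of life, well-being and care dependency from those who stay. The pre-post contrast could then partly reflect who remained to be measured. This is a rule about data collection, so it cannot simply be left to the analysis plan: values that were never collected can later be replaced only under assumptions that the data cannot test.

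**Working it through.** **1. The timing statements side by side**

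| Section | Second survey is due | Reading for someone who stops at month 2 |
|---|---|---|
| Study period | at 3-6 months, during the intervention | no longer in the intervention, so not due |
| Intervention | no formal follow-up after the intervention; reasons for discontinuing collected | reason recorded, no outcome |
| Outcomes, Patient perspective | 3-6 months from start of participation or enrolment | still due |

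The first two rows and the third lead to different data sets. Nothing in the article says outright that stoppers are surveyed, or that they are not.

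**2. Routes by which a post value can be lost**

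| Route | Intervention group | Control group 2 |
|---|---|---|
| Death, withdrawal of consent, non-response | yes | yes |
| Stopping the programme before the second survey | yes, on the Study period reading | no programme to stop |
| Exclusion on losing a criterion such as caregiver or participating insurer | yes, as stated | no such rule stated |

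Control group 2 is drawn from other insurers (Participants), and the Analysis section says that it shares the criteria on age, care level and region. The last two rows are the asymmetry.

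**3. The plan's own figure**

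The only computed sample size concerns hospitalization, the primary outcome: 20% versus 15%, power 90%, significance level 0.05. Taking the test as two-sided, without continuity correction:

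n = [1.960·√(2 × 0.175 × 0.825) + 1.282·√(0.20 × 0.80 + 0.15 × 0.85)]² / 0.05² = 1,212 per group

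The unpooled form gives 1,208.4, rounded up to 1,209. The stated 1,210 is reproduced. Recruiting 1,500 tolerates a loss of 1 − 1,210/1,500 = 19.3%. That allowance covers the primary outcome and explicitly includes deaths. It is not a forecast of survey loss by month 3-6 and serves below only as a generous input.

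**4. Illustration of size**

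Let d₁ and d₂ be the proportions lost in the intervention group and control group 2. Let D be how much worse, in SD of the change score, those lost fare than those who stay, taken as equal in both groups. With no true effect:

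- bias = (d₁ − d₂) × D
- SE = √[1/(1,500(1 − d₁)) + 1/(300(1 − d₂))]
- for d₁ = 0.193 and d₂ = 0, SE = √(1/1,210 + 1/300) = 0.0645 SD

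The article gives no SD, no survey loss by group and no D, so all three are assumptions. Cells show the bias in SD and, in brackets, the rejection rate of a nominal two-sided 5% test.

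| d₁ | d₂ | D = 0.3 | D = 0.5 | D = 0.8 |
|---|---|---|---|---|
| 19.3% | 0 | 0.058 (15%) | 0.097 (32%) | 0.154 (67%) |
| 19.3% | 10% | 0.028 (7%) | 0.0465 (11%) | 0.074 (20%) |
| 19.3% | 19.3% | 0 (5%) | 0 (5%) | 0 (5%) |
| 10% | 0 | 0.030 (8%) | 0.050 (12%) | 0.080 (24%) |

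If control group 2 loses more, the sign reverses: d₁ = 10%, d₂ = 19.3% and D = 0.5 give (0.10 − 0.193) × 0.5 = −0.0465 SD.

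**The case against.** The best defence is that the Outcomes section already anchors these assessments to entry. The phrase in the Study period section may then only mark calendar time, and the sentence on follow-up may only mean that nothing is measured once the project ends. SoSci Survey is a route outside the diary. This reading is possible, and it is why the point is an inconsistency with a risk attached rather than a proven loss. It does not remove the point. The Intervention section turns directly from no follow-up to the reasons given by those who discontinue, and no section says that they are still surveyed.

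A reader might go further and infer that the comparison becomes completers against everyone, to the intervention's advantage. The documents do not support that. Control group 2 can lose people through death, withdrawal or non-response. It is also asked weekly health questions without receiving the service, so its loss could be lower, equal or higher. Only those who stop before their second survey are affected; later stoppers keep their post value.

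It is also fair to say that analysis sets and the handling of missing data commonly sit in an analysis plan. No criticism is made of their absence here. The Limitations section names selection and response bias in general terms, but not this loss.

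**Conclusion.** The concern holds as a risk. The article times the second survey in two ways that do not agree. On the reading given by the Study period and Intervention sections, early stoppers have no post value, and the exclusion rule removes further intervention participants. Control group 2 has neither route as written, so loss on these secondary outcomes risks being differential and informative.

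Neither direction nor size can be established. A reader might take the top row of the illustration (rejection rates of 15% to 67%) as the expected error rate. It is not. It requires the whole 19.3% allowance, deaths included, to fall before the second survey, no loss at all in control group 2, and an assumed gap of 0.3 to 0.8 SD. With 10% similar loss in control group 2 the rates fall to 7% to 20%, and with equal informative loss the bias is zero. The primary claims-based outcomes are not touched by this point. The change is worth making because it is cheap and because uncollected values cannot be recovered.

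**What to change.** - **Study period:** align with the Outcomes section. The second survey is due 3-6 months after enrolment, whether or not the diary is still used, for everyone alive who has not withdrawn consent to be surveyed.
- **Data sources:** state that people who have stopped the diary receive this survey through SoSci Survey, which is already in use.
- **Intervention and Participants:** state that stopping the diary, or no longer meeting an inclusion criterion, may end the intervention but does not end this survey. Without the change in the Participants section, the exclusion rule would still remove people whom the revised schedule is meant to reach.

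The cost is a few sentences and a survey link for those who stop, with no new instrument, visit or staff. Only 36 participants had been enrolled when the article was submitted. The change removes loss caused by programme stopping or exclusion only as far as these people respond, and it does nothing about deaths. Response among stoppers will be incomplete, and the estimated benefit may turn out smaller.
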